### Interim analyses {21b}

We started performing statistical analysis when the samples reached 60. After the interim results are obtained, the primary investigator will determine whether the experiment will be continued.

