## Assignment of interventions: blinding

### Who will be blinded {17a}

All participants, subjects, and study monitors will be blinded until the trial is completed.

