## Statistical methods

### Statistical methods for primary and secondary outcomes {20a}

Data analysis will be completed using the Statistical Packages of Social Sciences software (version 24.0). Qualitative indicators will be described in terms of frequency tables, percentages, or component ratios, whereas quantitative measures will be described in terms of mean, median, lower quartile (Q1), upper quartile (Q3), minimum, and maximum. For the comparative analysis of the two groups, the chi-square test, Fisher’s exact probability method, and Wilcoxon rank and inspection will be applied for qualitative data and *t* test will be applied for quantitative data, while the *t* test will be applied for quantitative data with normal distribution. Homogeneity test of variance will be conducted among the groups, with a cutoff level of 0.05, and the Satterthwaite method will be used to conduct the corrected *t* test when the variance is uneven. If the data do not follow normal distribution, the Wilcoxon rank test and inspection will be performed. The two-sided test will be uniformly used in the hypothesis test, and the test statistics and their corresponding *P* values will be provided, with *P* values ≤ 0.05 considered statistically significant and *P* values ≤ 0.01 considered highly statistically significant.

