## Oversight and monitoring

### Composition of the coordinating center and trial steering committee {5d}

The coordinating center is the Department of Cardiology of Longhua Hospital Affiliated to Shanghai University of Traditional Chinese Medicine, and the head of the department is the principal investigator, who will conduct the trial, identify potential recruits, obtain consent, and report to the trail steering committee. The trial steering committee is the Good Clinical Practice office of Longhua Hospital, affiliated with the Shanghai University of Traditional Chinese Medicine. The responsibilities include agreement and amends to the protocol, receiving reports from the coordinating center, supervising the trial, reviewing trial progress, and reviewing the paper for publication. Meetings are conducted every 6 months.

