### Composition of the data monitoring committee, its role and reporting structure {21a}

The data monitoring committee (DMC) includes a researcher, who will not be involved in the data collection, data manager, biostatistician, and ethicist (independent from the sponsor and free from competing interests). The DMC will conduct periodic interim evaluations and discontinue the trial if there are obvious differences between the two groups.

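### The investigator and the DMC are each given the decision to stop, the only stopping criterion is not operational, and the full 0.05 is kept for the final test

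*Protocol article*

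**What the plan says.** The section Interim analyses {21b} consists of two sentences. The first, in the past tense, is "We started performing statistical analysis when the samples reached 60". The second gives the decision that follows to the investigator: "After the interim results are obtained, the primary investigator will determine whether the experiment will be continued". It states no purpose (efficacy, futility or safety), endpoint, threshold or restriction on who sees the results.

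The section on the data monitoring committee {21a} says: "The DMC will conduct periodic interim evaluations and discontinue the trial if there are obvious differences between the two groups".

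Statistical methods {20a} sets one rule for all testing: "The two-sided test will be uniformly used in the hypothesis test", with P "values ≤ 0.05 considered statistically significant". Sample size {14} uses alpha 0.05 and 80% power and mentions no interim analysis.

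The section on the coordinating center {5d} describes the principal investigator as the person "who will conduct the trial, identify potential recruits, obtain consent". The Discussion describes the primary outcome, cardiac function, as subjective and accepts that some bias remains. Under Who will be blinded {17a} the protocol states: "All participants, subjects, and study monitors will be blinded until the trial is completed".

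**The concern.** Two bodies hold the same decision. Under {21b} there is one look, at 60 patients, and the investigator decides. Under {21a} there is an unstated number of looks, and the DMC stops the trial. If they disagreed, the protocol would not say whose decision counts. The DMC's criterion, an obvious difference, gives no endpoint, statistic or limit, so two competent committees could reach opposite decisions on the same data.

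Two things are at stake. First, if an interim difference can end the trial with a claim of efficacy, and the final test still uses the full 0.05, the chance of a false-positive result exceeds 5% by an amount that depends on a threshold the protocol does not give. Second, the person deciding from the interim results also finds and consents later patients. Knowing the emerging difference could affect whom that person approaches and how the later part of the trial is run, and a subjective primary outcome is more open to such influence than an objective one.

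**Working it through.** **1. The stated sample size uses all of alpha.** Inputs from Sample size {14}: 93.3% v 73.3%, alpha 0.05, power 80%. With the unpooled normal formula and a two-sided test:

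n = (1.960 + 0.842)² × (0.933 × 0.067 + 0.733 × 0.267) / 0.20² = 7.849 × (0.0625 + 0.1957) / 0.04 = 50.7, so 51 per group.

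This reproduces the protocol's 51. Then 51 × 1.2 = 61.2, given as 61 per group and 122 in total. Nothing is reserved for an interim look.

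**2. Information at the look.** Taking 60 as the total across both groups, the information fraction t is 60/122 = 0.49. Against the 2 × 51 = 102 patients needed before loss, it is 60/102 = 0.59.

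**3. Overall two-sided type I error.** Under the null hypothesis, the interim and final statistics Z₁ and Z₂ are approximately bivariate normal with correlation √t (0.701 at 60/122, 0.767 at 60/102). The overall error is

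1 − P(|Z₁| < c₁ and |Z₂| < c₂),

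with c₂ = 1.96 for a final test at 0.05. The interim threshold is not stated, so it is varied:

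| Interim threshold for an efficacy stop | Overall error, t = 60/122 | Overall error, t = 60/102 |
|---|---|---|
| 0.05 | 8.3% | 8.0% |
| 0.01 | 5.5% | 5.4% |
| 0.005 | 5.2% | 5.1% |
| 0.001 | 5.02% | 5.01% |
| No efficacy stop (futility only) | at most 5% | at most 5% |

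A simulation of two chi-square tests on a binary outcome (400,000 runs, null response rates 73.3% and 83.3%) agrees with the first row: 8.3% to 8.4% for looks at 30 and 61 per group, and 8.0% to 8.1% for 30 and 51.

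**4. Boundaries that hold 5% at t = 60/122.** A threshold of 0.001 at the interim with 0.05 at the end gives 0.0502 overall. The Lan-DeMets O'Brien-Fleming-type spending function gives 4 × [1 − Φ(2.241/0.701)] = 0.0028 at the interim, which leaves 0.0491 for the final test and 0.0500 overall.

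**5. The two sections side by side.**

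| | Interim analyses {21b} | Data monitoring committee {21a} |
|---|---|---|
| When | at 60 patients | periodically, number not given |
| Who decides | primary investigator | DMC |
| Criterion | none | obvious difference between groups |

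No reading lets both columns stand as the rule for one decision.

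**The case against.** The strongest reply is that {21b} never calls the look an efficacy look. It mentions a statistical analysis and a decision, and does not say that results are compared by group. The 0.05 in {20a} is not tied to the interim. Boundaries are often placed in an analysis plan or DMC charter, neither of which is shown, so their absence from an article is not in itself a fault. This reply stands as far as the size goes: 8.3% is conditional, and a reader who took it as the trial's actual error rate would go beyond the text. It does not remove the conflict between {21b} and {21a}, because a boundary written elsewhere would still leave two bodies with the same decision.

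A reader might also infer that the look breaks the blind. The documents do not support that. {21b} does not say that results are shown by group, {17a} does not name investigators among those blinded, and {16c} denies researchers access to the random sequences. Knowing a group-level difference does not by itself reveal any patient's allocation, and no section says that the principal investigator grades cardiac function. What remains is the risk of operational bias.

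Finally, a reader might count every six-monthly DMC meeting as a further efficacy test and arrive at a much larger error. The section on auditing {23} says those meetings review trial conduct, and {21a} gives no number of interim evaluations, so no such figure can be derived.

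**Conclusion.** The point holds and should be settled before any further comparative result is produced. It is certain from the text that {21b} and {21a} conflict on who decides and when, that the one criterion is not operational, and that neither the sample size nor the significance level allows for an interim look.

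The effect on type I error is conditional: up to about 8.3% for the look at 60 if it permits an efficacy stop at 0.05, falling to about 5.0% with a threshold of 0.001, and no inflation with futility-only stopping. These figures assume that 60 is the total across both groups, that there is one interim look, and that the test statistics are approximately normal.

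The bias concern rests on an inference: a decision to continue on efficacy grounds needs a comparison between groups, and {21b} has no safeguard that would keep this from an investigator who is still recruiting.

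**What to change.** Replace {21b} and the stopping sentence in {21a} with a single rule:

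- There is one comparative interim analysis at 60 patients, prepared by a statistician outside the study team and seen only by the DMC.
- The DMC recommends stopping for efficacy only at two-sided P < 0.001, with the final test at 0.05 (overall about 0.0502). The alternative is a Lan-DeMets O'Brien-Fleming-type boundary, about 0.0028 at the interim and 0.0491 at the end for 60/122. Name the choice in the protocol.
- Other DMC reviews cover safety and conduct only.
- The investigator learns only whether to continue or stop.

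If the look has not been done, the cost is wording. The DMC already includes a biostatistician, and the final threshold hardly moves.

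The past tense in {21b} suggests that the look may already have been done. In that case a boundary chosen now does not repair it. Report when it was done, what was compared, who saw it and what was decided. State that the final P value follows an interim look without a prespecified boundary, give the conditional type I error (up to about 8.3%), and keep any further comparative results within the DMC. The cost is then a disclosed limitation on the primary result as well as the change of wording.

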### Methods for additional analyses (e.g., subgroup analyses) {20b}

We will perform subgroup analysis by gender or age in the future.

### Methods in analysis to handle protocol non-adherence and any statistical methods to handle missing data {20c}

We will perform per-protocol and intention-to-treat analyses. Participants with poor compliance (compliance of experimental drug < 80%) or those no longer receiving medication and undergoing testing during the study will be excluded from the per-protocol analysis. Researchers will be advised to take active measures to complete the last test if the participants drop out of the trial or are lost to follow-up for the intention-to-treat analysis. Missing data will be imputed using a multiple imputation procedure via chained equations.

### Plans to give access to the full protocol, participant level-data, and statistical code {31c}

The complete protocol, participant level data, and statistical code are available on request from the corresponding author.

## Oversight and monitoring

### Composition of the coordinating center and trial steering committee {5d}

The coordinating center is the Department of Cardiology of Longhua Hospital Affiliated to Shanghai University of Traditional Chinese Medicine, and the head of the department is the principal investigator, who will conduct the trial, identify potential recruits, obtain consent, and report to the trail steering committee. The trial steering committee is the Good Clinical Practice office of Longhua Hospital, affiliated with the Shanghai University of Traditional Chinese Medicine. The responsibilities include agreement and amends to the protocol, receiving reports from the coordinating center, supervising the trial, reviewing trial progress, and reviewing the paper for publication. Meetings are conducted every 6 months.

### Composition of the data monitoring committee, its role and reporting structure {21a}

The data monitoring committee (DMC) includes a researcher, who will not be involved in the data collection, data manager, biostatistician, and ethicist (independent from the sponsor and free from competing interests). The DMC will conduct periodic interim evaluations and discontinue the trial if there are obvious differences between the two groups.

### Adverse event reporting and harms {22}

Adverse events will be recorded and reported to the researchers, including the timing, severity and duration, actions taken, and outcomes. Zhigancao Tang granules may cause diarrhea, abdominal distension, dizziness, and anaphylaxis. The researchers will record the adverse events and decide whether to terminate the treatment based on the patient’s condition and report the same to the DMC and ethics committee. Other unintended effects of trial interventions or trial conduct will also be reported.

### Frequency and plans for auditing trial conduct {23}

The project management group will meet to review trial conduct every three months, and the trial steering group, DMC, and ethics committee will meet to review trial conduct every 6 months.

### Plans for communicating important protocol amendments to relevant parties (e.g., trial participants, ethical committees) {25}

When there are significant changes in the study process, we will notify the sponsor firstly, and then the center will be notified by the principal investigator, and an amended copy of the protocol will be sent to the investigator site file to be added. Any breach of this protocol will be fully documented using the breach report form. Then, the protocol will be updated in the clinical trial registry.

### Dissemination plans {31a}

The final data will be submitted to the Shanghai Science and Technology Committee in the form of a research report by the researchers after completion of the study. The results will be published in a peer-reviewed academic journal to share the findings with the general public and healthcare professionals.

## Discussion

HFpEF is a clinical syndrome classified as heart failure with a reduced or preserved ejection fraction. However, it remains debatable if these are two different entities or different stages of a single process [14]. The prevalence of HFpEF increases with age, and previous studies have shown that it is more common in women than in men of the same age [15–17]. The pathophysiology of HFpEF remains poorly understood and has several phenotypes, which makes its diagnosis and treatment considerably challenging [4]. HFpEF has garnered increasing attention in recent years owing to the high mortality rate reported. Furthermore, diastolic dysfunction is a hallmark of HFpEF, which is associated with adverse prognosis [18, 19]. Although there have been several large prospective RCTs such as PEP-CHF, CHARM-Preserved, I-PRESERVE, TOPCAT, Aldo-DHF, and SENIORS, therapies for reducing mortality in HFpEF are yet to be reported [20–25].

Zhigancao Tang has been used traditionally for treating arrhythmia, viral myocarditis, and ischemic cardiomyopathy [26–28]. Several clinical trials have shown that Zhigancao Tang can improve symptoms such as heart palpitations, shortness of breath, and fatigue in patients with premature ventricular contractions [9]. A case report suggested that modified Zhigancao Tang could improve exercise tolerance and alleviate pulmonary edema and cardiomegaly in an 18-year-old adolescent male with congestive heart failure induced by chemotherapy [29]. Furthermore, Zhigancao Tang has been reported as the most frequently used Chinese herbal prescription formula for treating heart failure, as it can supply Yang-Qi, nourish the Ying-blood, and strengthen the heart spirit to relieve symptoms of heart dysfunction when co-administered with standard anti-heart failure treatments [30].

Based on our analysis of literature in PubMed, Embase, Cochrane Library, China National Knowledge Infrastructure, and Clinical Trials up to April 2020, we found that no large randomized clinical trial have been conducted to evaluate the safety and efficacy of Zhigancao Tang in treating HFpEF. To the best of our knowledge, this is the first randomized, double-blind, placebo-controlled trial to investigate the effectiveness and safety of Zhigancao Tang. First, a double-blinded study and a placebo were designed to avoid bias owing to subjectivity, personal preferences, and placebo effects. Second, since HFpEF has several phenotypes, patients with atrial fibrillation were excluded to select a specific patient population. However, this study has a few limitations. This is a single-center trial conducted in China. Considering the large population size in China, this study may not adequately represent patients from other regions. Moreover, the primary outcome was set as cardiac function, which is a subjective indicator; therefore, a certain bias remains.

This randomized, double-blind, placebo-controlled trial will evaluate the clinical efficacy and safety of Zhigancao Tang granules for treating HFpEF and its efficacy in improving cardiac function, clinical symptoms, quality of life, and exercise capacity in patients with HFpEF; the trial will provide useful data for a novel strategy for HFpEF treatment.

## Trial status

The protocol version number and date were V1.0 and April 20, 2020, respectively. Patient recruitment has commenced in April 2019 and will end in April 2022.

## Abbreviations

ACC/AHA: American College of Cardiology/American Heart Association
ACEI: Angiotensin-converting enzyme inhibitors
ANP: Atrial natriuretic peptide
ARB: Angiotensin receptor blocker
ARNI: Angiotensin receptor neprilysin inhibitor
CRFs: Case report forms
ESC: European Society Cardiology
GCP: Good Clinical Practice
HFpEF: Heart failure with preserved ejection fraction
LVEDD: Left ventricular end-diastolic diameter
LVEF: Left ventricular ejection fraction
LVESD: Left ventricular end-systolic diameter
MLHFQ: Minnesota Living with Heart Failure questionnaire scale
NT-proBNP: N-terminal pro-brain natriuretic peptides
NYHA: New York Heart Association
